# **Chapter 1: Introduction to the IMPACT Research Study**

## 1.1 INTRODUCTION

### 1.1.a SUMMARY

The Initiate and Maintain Physical Activity in Clinics (IMPACT) Study is a research study utilizing physical activity in an intervention for Type 2 diabetes (T2DM) patients in a clinical setting. The study will compare structured group exercise within the clinic for T2DM patients compared to usual care, which does not involve structured group exercise within the clinic setting. The main purpose of the study is to determine the optimal and feasible level of frequency of structured contact needed in a clinical setting for adult T2DM patients to initiate and maintain physical activity recommendations long-term.

### 1.1.b BACKGROUND

Type 2 diabetes (T2DM) affects 25.8 million people in the United States and the prevalence and incidence is increasing. Research has shown that physical activity is beneficial in T2DM management with lower glycemic control achieved when patients follow a structured exercise program in a research setting. Given the known benefits of dietary changes in T2DM, nutrition referrals are common in current clinical practice. Despite the similarly known benefits of exercise, physical activity referrals are not readily available in the clinical setting. According to the current American Diabetes Association (ADA) guidelines, individuals with T2DM should engage in at least 150 minutes of moderate-intensity aerobic activity per week and resistance exercises at least 2 times per week. However, approximately 38 percent of T2DM patients do not exercise at recommended levels and 31 percent do not exercise at all.

A recent meta-analysis of randomized controlled trials (RCTs) demonstrated that highly structured physical activity training regimens were effective in reducing glycosylated hemoglobin A1c (HbA1c) levels in individuals with T2DM, while physical activity advice alone had no effect on HbA1c. Of the 23 RCTs which tested structured training programs, most consisted of at least three structured sessions per week, and ranged in length from 3 – 12 months. While the efficacy of such intensive physical activity interventions among individuals with T2DM in a highly structured research setting has been proven, practical approaches to translate and extend these findings into the clinical setting are needed. Less intensive approaches, such as physical activity advice delivered by physicians, have been tested in clinical settings, and are not effective in increasing physical activity.

## 1.2 STUDY RESEARCH STRATEGY

### 1.2.a STUDY SIGNIFICANCE

The efficacy of intensive physical activity interventions, consisting of 3 – 5 structured sessions per week among T2DM individuals in a research setting has been proven. Less intensive interventions, such as physical activity advice only, have been attempted in research and

clinical settings are known to be ineffective. Translational studies are needed to test innovative and practical adaptations of evidence-based interventions, in order to legitimize and integrate physical activity as a part of standard clinical practice.

## **IMPORTANCE OF DIET AND PHYSICAL ACTIVITY IN T2DM MANAGEMENT**

### **Nutrition Counseling in Clinical Practice**

The efficacy of nutrition counseling for T2DM was first recognized in clinical trials and with its effectiveness later proven in translational studies. In December 1999, the Institute of Medicine released a report confirming the clinical- and cost-effectiveness of nutrition counseling for T2DM. As a result, nutrition counseling became a covered Medicare benefit, and all major insurers followed this reimbursement practice. In 2002, the American Diabetes Association (ADA) recognized the “complexity of nutrition issues” and recommended that specialized services be offered, over and above routine physician office visit counseling, to provide adequate support. For over a decade, nutrition counseling has been successfully institutionalized within the healthcare environment. At the Palo Alto Medical Foundation (PAMF), nearly half of all newly diagnosed T2DM patients receive referrals for specialized diabetes diet education services.

### **Limited Physical Activity Resources in Clinical Practice**

The efficacy of physical activity in T2DM patients is well known. Structured exercise has been shown to improve glycemic control and reduce the risk of cardiovascular disease. While the proven value of aerobic exercise is undisputed, resistance training may be particularly helpful for T2DM patients, as improved muscle function and growth may increase muscle glucose storage, alter insulin sensitivity via the expression of the GLUT-4 transporter, and thereby improve glycemic control. The combination of both aerobic and resistance training exercise has been found to provide the greatest reduction in glycosylated hemoglobin A1c (HbA1c) levels in T2DM patients, compared to either aerobic or resistance training alone. Therefore, the current evidence-based ADA guidelines recommend that individuals with T2DM perform at least 150 minutes per week of moderate-intensity aerobic physical activity and resistance training at least two times per week.

A recent meta-analysis of 47 randomized controlled trials in T2DM has confirmed that structured exercise lowers HbA1c, and physical activity advice alone is ineffective. Despite these findings, structured exercise programs for patients with T2DM are not currently available in clinical settings, and doctors and patients are left to rely on physical activity advice only.

Furthermore, previous research examining physical activity counseling within the clinical setting has shown that physician counseling for physical activity occurs in less than 30% of ambulatory care visits. The Activity Counseling Trial (ACT), a randomized control trial (RCT) designed to compare the effects of two physical activity counseling interventions with recommended physician advice, demonstrated that physician advice and written educational materials did not increase physical activity in patients, both at 6 and 24 month follow-up, compared to baseline. Meta-analysis has confirmed the lack of efficacy of physical activity advice only.

Cardiac rehabilitation, which includes physician prescribed exercise training, is integral to the comprehensive care of patients with cardiovascular disease and is a covered Medicare benefit. Though physical activity is similarly beneficial for T2DM patients, structured exercise programs have not been developed to assist physicians and patients in a clinical setting.

### **RATIONALE OF TREATMENT AND SELECTION OF INTENSITY DOSES**

The current ADA guidelines recommend that individuals with T2DM perform at least 150 minutes per week of moderate-intensity aerobic physical activity and, in the absence of contraindications, perform resistance training at least two times per week, targeting all major muscle groups. The 2006 ADA guidelines also acknowledge the key role of supervision and contact for resistance training, stating that: “To ensure resistance exercises are performed correctly, maximize health benefits, and minimize the risk of injury, we recommend initial supervision and periodic re-assessments by a qualified exercise specialist, as was done in the clinical trials.” The incidence of injury in high-intensity structured exercise trials such as the Health Benefits of Aerobic and Resistance Training in individuals with T2DM (HART-D) study was extremely low (no serious adverse events occurred during exercise training), given that skilled professionals were on site and available to teach proper technique and supervise participants. Conversely, unsupervised physician advice programs, such as the ACT, have yielded much higher rates of musculoskeletal injury (30% annually). These findings underscore the importance of supervision in preventing injury during exercise. Thus, based on the ADA guidelines and previous studies, the IMPACT study has chosen to implement a structured physical activity program based on the HART-D intervention within the clinical setting. Prevention of injury will likely result in longer term adherence to exercise recommendations, and, ultimately, will result in better clinical outcomes.

There is some variation in the frequency of contact and the length of intervention in studies of physical activity and exercise in T2DM patients. Intensive lifestyle interventions have shown that once a week structured contact, in the form of group meetings and individual counseling sessions on diet and exercise, is effective in lowering HbA1c. However, there are no studies of once-weekly interventions of structured physical activity alone. Studies of structured physical activity interventions have differed in dose ( $\leq 150$  min/week vs.  $> 150$  min/week), and the level HbA1c change differs by the dose of structured physical activity (see Table 1). Most large, recent, and well-designed studies of structured exercise have used frequencies of three times per week, lasting 3-12 months in duration.

Based on previous studies, the IMPACT study has selected a frequency of one (60 min) versus three (180 min) times per week, and an intervention length of 6 months. Based on previous studies at PAMF and literature review, we believe that a minimum of once-weekly contact is necessary to effect significant behavioral changes. Thrice-weekly contact has been shown to be most effective for structured exercise in a research setting. It is unknown whether similar effect sizes can be achieved in the clinical setting, with real-world patients.

### **1.2.b STUDY INNOVATION**

### **TRANSLATING CLINICAL TRIAL RESULTS TO CLINICAL PRACTICE**

Based on previous studies, determining the correct intervening dosage is essential for effectiveness of behavioral change. While higher dosage interventions work in a research setting, the effectiveness of the dosage level translated into clinical setting remains unknown. An innovative aspect of the IMPACT study is the integration of cost effectiveness, and the consideration of both clinical and patient-centered outcomes in this analysis. Findings from this study will be used to help other healthcare organizations fully realize the investment already made in physical activity research, by translating efficacious clinical trial interventions into clinics.

### **UTILIZATION OF ELECTRONIC HEALTH RECORD AND PATIENT PORTAL**

The Health Information Technology (HITECH) Act calls for the rapid adoption and implementation of electronic health records (EHRs) by medical providers, hospitals, and ambulatory care institutions throughout the country, with the goal of all providers adopting EHR by 2014. SHC has used the EpicCare EHR system since 2008 and is very experienced in the traditional uses of EHR in patient care. The IMPACT study will use the EHR as a tool to operationalize our intervention.

## Chapter 2: Overview of the Study

## 2.1 STUDY PURPOSE AND GOAL

### 2.1.a STUDY PURPOSE

Translational studies are needed to improve the uptake and effectiveness of physical activity recommendations among the general clinical T2DM patient population. While most other translational studies have explored adapting physical activity interventions to other community settings, the IMPACT study intends to institutionalize physical activity resources within a clinical setting and integrating it with medical care, as this conveys an implicit endorsement of physical activity by a patient's health care team.

### 2.1.b STUDY GOAL

The goal of IMPACT is to translate efficacious structured physical activity interventions in the clinical setting. Specifically, the study seeks to formalize physical activity as an essential part of T2DM self-management by institutionalizing it within a healthcare setting and empowering patients through structured group exercise therapy.

### 2.1.c STUDY INTERVENTION

With the addition of resistance training to the 2006 ADA guidelines, it is especially important to provide supervision and support for exercise, to prevent injury and maximize health benefits. In order to address these needs, IMPACT will implement a three-arm RCT to compare the clinical and cost-effectiveness of adding a specialized physical activity component for T2DM patients in a healthcare setting. The intervention will be fully integrated with and supported by the Electronic Health Record (HER). Eligible patients will be recruited, consented, and randomized to one of three study arms. Details of the study intervention will be discussed in a later section.

### 2.1.d STUDY AIMS

The specific aims of IMPACT study includes: (1) Clinical Effectiveness, (2) Patient-Centered Outcomes, and (3) Cost-Effectiveness.

#### **Clinical Effectiveness**

The IMPACT study is to evaluate clinical effectiveness through comparing outcome measures of the three study arms (Arm 1 vs Arm 2 vs Arm 3). The primary outcome will be improvements in Hemoglobin A1c (HbA1c) levels in study participants. Process outcome measures will include changes in physical appearance (ie. body weight, waist circumference), physical fitness (ie. blood pressure, VO2 max, grip strength), and self-reported physical activity level.

#### **Patient-Centered Outcomes**

The IMPACT study is to evaluate patient-centered outcomes using self-reported questionnaires. Satisfaction with the IMPACT exercise program will be compared between the two

experimental study arms (Arm 1 vs Arm 2). Self-reported quality of life will be compared across all three study arms (Arm 1 vs Arm 2 vs Arm 3).

### **Cost-Effectiveness**

The IMPACT study is to evaluate cost-effectiveness based on clinical outcomes and quality of life. This will involve comparing the average cost and outcomes and determining the incremental cost-effectiveness ratio (ICER) for each study arm (Arm 1 vs Arm 2 vs Arm 3).

## **2.2 STUDY DESIGN**

### **2.2.a RANDOMIZED CONTROLLED TRIAL STUDY**

The IMPACT study will implement a three-arm randomized controlled trial (RCT). Of the three study arms, two will be experimental groups with structured exercise sessions (once-weekly or thrice-weekly) as the designed intervention. The remaining study arm will serve as the control group. The study randomization software will assign each eligible study participant into one of three study arms.

#### **Arm 1: Once-Weekly Group Exercise Session (Experimental Group)**

The first arm of the IMPACT study requires study participants to attend one on-site group exercise session per week. Each exercise session consists of aerobic and resistance training. In addition, study participants are to complete assigned surveys, update exercise log, and attend a total of six study visits.

#### **Arm 2: Thrice-Weekly Group Exercise Sessions (Experimental Group)**

The second arm of the IMPACT study requires study participants to attend three on-site group exercise sessions per week. Participants are to attend one aerobic only session and two combined, aerobic and resistance, sessions. In addition, study participants are to complete assigned surveys, update exercise log, and attend a total of six study visits.

#### **Arm 3: Usual Care (Control Group)**

The third arm of the IMPACT study does not required study participants to attend any group exercise sessions. Study participants are to continue with current T2DM management and seek care from their personal healthcare provider. Study participants within this study arm are expected to attend a total of six study visits.

### **2.2.b LONGITUDINAL STUDY**

IMPACT is a longitudinal study designed to track study participants over a course of 2.5 years. Once study participants have been determined eligible and are officially enrolled into the research study, they will begin study phase 1 for six months. After the six months, study phase 2 will begin and last for two years.

### Phase 1: Initiate

The first phase of IMPACT (Phase 1) is to initiate physical activity through group exercise sessions for study participants within experimental groups (Arm 1 and Arm 2). The control group (Arm 3) is expected to attend study visits only.

Phase 1 is to take place over a six-month period during which all participants are to attend three study visits (baseline, 3-month, and 6-month).

### Phase 2: Maintain

The second phase of IMPACT (Phase 2) is to follow-up with study participants. Experimental study participants (Arm 1 and Arm 2) are monitored to determine whether physical activity is being maintained. The control group (Arm 3) is expected to attend study visits only.

Phase 2 is to take place over a two-year period during which all participants are to attend three study visits (12-month, 18-month, and 30-month).

### Study Design Diagram

|     |   | Phase 1: Initiate |                |                                  |                |                | Phase 2: Maintain |                |                |
|-----|---|-------------------|----------------|----------------------------------|----------------|----------------|-------------------|----------------|----------------|
| ARM |   | V1                |                | V2                               |                | V3             | V4                | V5             | V6             |
| 1   | R | O 1    | X 1 | O 2                   | X 1 | O 3 | O 4    | O 5 | O 6 |
| 2   | R | O 1    | X 2 | O 2                   | X 2 | O 3 | O 4    | O 5 | O 6 |
| 3   | R | O 1    |                | O 2                   |                | O 3 | O 4    | O 5 | O 6 |
|     |   | R: Randomization  |                | O: Observations/Outcome Measures |                |                | X: Intervention   |                |                |

### 2.2.c COHORT STUDY

IMPACT is a cohort study designed to have multiple participant groups over the course of the study. With an anticipated study population of 345 participants.

Each group is expected to commence 15 days apart. The time-period between each cohort group is designed to allow participants in the intervention arms to attend orientation sessions before they start their respective exercise regimen.

## 2.3 STUDY HYPOTHESES

### 2.3.a PRIMARY HYPOTHESIS

The primary hypothesis for the IMPACT Study is that structured physical activity interventions in a clinical setting will be efficacious in improving T2DM control, improving physical fitness and increasing physical activity compared to usual T2DM care.

### 2.3.b SECONDARY HYPOTHESES

Due to the depth and intricacy of the research topic and purpose, IMPACT proposes multiple secondary hypotheses for the study. The hypotheses are categorized according to the specific study aims.

#### **Clinical Effectiveness**

1. By the end of Phase 1, experimental study participants (Arm 1 & Arm 2) who adhered to their group exercise schedule should have greater improvements in primary outcomes compared to non-experimental study participants (Arm 3).
  - a. Improvements in primary outcomes include reduction in HbA1c levels, increase in VO2 max levels, and increase in self-reported physical activity levels.
2. By the end of Phase 1, experimental study participants who attended thrice-weekly group exercise sessions (Arm 2) should have greater improvements in primary outcomes compared to experimental study participants who attended once-weekly group exercise sessions (Arm 1).
3. By the end of Phase 2, experimental study participants (Arm 1 & Arm 2) who maintained their exercise schedule should have improved primary outcomes compared to non-experimental study participants (Arm 3).
4. By the end of Phase 2, experimental study participants who maintained thrice-weekly exercise sessions (Arm 2) should have greater improvements in primary outcomes compared to experimental study participants who maintained once-weekly exercise sessions (Arm 1).

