## **6.2 DATA ANALYTICAL METHODS**

### **6.2.a DATA ANALYSIS PLAN**

Statistical analyses will investigate clinical effectiveness of structured physical activity regimens across varying frequencies. The main statistical approach will be to date-match outcomes to concomitant exercise regimens, then to examine univariate and multivariate associations with changes in clinical outcomes, patient-centered outcomes, and cost. Statistical significance will be determined at  $P < 0.01$ , a stricter value due to the expected number of models used, or with other adjustments for multiple comparisons when applicable. Statistical analyses will be performed using SAS® (Cary, NC), and supplemented with STATA or Splus for methods not available in SAS®.

Study participants who are not able or willing to continue with the randomized frequency of intervention will be treated as loss to follow-up and only data obtained while in the assigned protocol will be used in the primary analysis (intention-to-treat). Since participants and non-participants continue to receive care within the healthcare system contemporaneously during the research study, IMPACT will obtain interstitial outcome data and complete clinical narrative through observational data available in the EHR. The statistical analysis will be conducted by Senior Statistician/s with the guidance of Biostatistical Consultant [name].

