## **STUDY AIM 1: CLINICAL EFFECTIVENESS**

### **Research Questions**

1. Does a thrice-weekly, structured exercise regimen have greater reduction in HbA1c than a weekly contact exercise regimen? How do these interventions compare to usual care?
2. Are the same improvements observed for process measures (i.e., VO2 max and self-reported physical activity)?

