### **Primary Outcomes and Process Measures**

Primary outcomes and process measures will be compared between the three intervention arms (weekly, thrice-weekly, usual care). Primary outcomes include absolute change in percent HbA1c, and process measures include change in VO2 max and self-reported physical activity. Adherence will be defined as attending more than 80% of assigned structured exercise sessions, and will be used as a covariate for stratification or adjustment.

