## **6.2.b POWER AND SAMPLE SIZE**

The primary analyses for this study will be comparing the clinical outcomes, patient-centered outcomes, and cost effectiveness of structured exercise regimens across varying frequencies (once vs. thrice-weekly, compared to usual care). For Specific Aim 1, overall change in baseline of outcome values will be examined (e.g. HbA1c, VO2max, physical activity). By the algebraic properties of log and variance, we estimated difference in groups as  $\log(\text{HbA1c}_1) - \log(\text{HbA1c}_2) = \log(\text{HbA1c}_1 / \text{HbA1c}_2)$ , and  $\text{SD}(\log(\text{HbA1c})) = \text{SD}(\text{HbA1c}) / \text{mean}(\text{HbA1c})$ . A two-sample *t*-test between means, Bonferroni adjusted  $\alpha = 0.05/3 = 0.016$ , assuming normality of  $\log(\text{HbA1c})$ , equal group variances, and a baseline mean HbA1c of 6.5%, we will have 80% power to detect a 0.5% point difference in HbA1c with 92 patients/arm. Accounting for a 20% attrition, this will require 115/arm, 345 patients total.

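### The protocol gives three incompatible accounts of what is primary, fixes no primary visit, and is sized at 0.05/3 but tested at P<0.01

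*Protocol*

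**What the plan says.** On the outcome, the protocol speaks in three ways.

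- Section 2.1.d (Clinical Effectiveness) names one: "The primary outcome will be improvements in Hemoglobin A1c (HbA1c) levels in study participants". Fitness and activity are listed there as process measures. Section 6.2.a agrees, both under sub-group analyses and under Study Aim 1: "Primary outcomes include absolute change in percent HbA1c, and process measures include change in VO2 max and self-reported physical activity".
- Section 2.3.b (Clinical Effectiveness) uses the plural: "Improvements in primary outcomes include reduction in HbA1c levels", and the list goes on to VO2 max and self-reported activity. The primary hypothesis in section 2.3.a covers the same three domains. It holds that structured exercise in the clinic "will be efficacious in improving T2DM control, improving physical fitness and increasing physical activity compared to usual T2DM care", with no rule on whether all or any must improve.
- Section 6.2.b opens wider still: "The primary analyses for this study will be comparing the clinical outcomes, patient-centered outcomes, and cost effectiveness".

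On timing, neither section 2.3.a nor the sample size names a visit. Section 2.3.b applies its primary outcomes at the end of Phase 1 (6 months) and again at the end of Phase 2 (30 months), under the heading of secondary hypotheses.

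On significance, section 6.2.a sets P<0.01, described as "a stricter value due to the expected number of models used, or with other adjustments for multiple comparisons when applicable". Section 6.2.b sizes HbA1c at 0.05/3 (printed as 0.016) and uses the same level again for satisfaction and quality of life.

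**The concern.** A confirmatory trial needs one statement of what decides it, and here the sections disagree. Suppose HbA1c shows no difference but self-reported activity improves: section 2.1.d calls that a failure on the primary outcome, while section 2.3.b lets it be reported as a primary-outcome improvement. Suppose an HbA1c effect at 6 months has gone by 30 months: nothing says which visit decides. An analyst who has seen the data could choose the favourable reading and cite the protocol for it.

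The two significance levels compound this. Neither is tied to a named family of tests, and the power statement uses the more lenient of the two.

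**Working it through.** **1. The plan's own figures.** The attrition step reproduces: 92/(1 - 0.20) = 115 per arm, and 3 x 115 = 345. The 92 per arm cannot be reproduced directly because no SD is given, but it can be solved for:

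- effect on the log scale: ln(7.0/6.5) = 0.0741
- n per arm = 2 x SD^2 x (z_alpha/2 + z_power)^2 / effect^2
- at two-sided 0.05/3: 2.394 + 0.842 = 3.236
- SD(log) = 0.0741 x sqrt(92/2) / 3.236 = 0.155, and 0.155 x 6.5 = about 1.0 HbA1c point

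So 92 per arm is coherent if the SD is about 1.0 point. That value is an inference, not a stated input.

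**2. Power at the level set for the analyses.** With the same n, effect and implied SD, two-sided 0.01 needs z = 2.576:

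- from 0.05/3: 3.236 - 2.576 = 0.660, power 74.5%
- from the printed 0.016: 3.251 - 2.576 = 0.675, power 75.0%

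This depends only on the claim of 80% power at 0.05/3, whatever the SD. To restore 80% at 0.01 would take 92 x (3.417/3.236)^2 = about 103 evaluable per arm (102 if the printed 0.016 is the starting point).

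**3. Family-wise error if any one success counted.** For k independent tests it is 1 - (1 - alpha)^k. This gives 4.9%, 14.0% and 26.1% for k = 3, 9 and 18 at 0.05/3, and 3.0%, 8.6% and 16.5% at 0.01. The tests are not independent, because pairwise contrasts share arms and outcomes correlate. The rates were therefore simulated: 400,000 null trials, three equal arms, all pairwise contrasts, and a common correlation across outcomes and visits. The protocol gives no correlation, so the range runs from 0.8 (lower figure) to 0 (higher figure).

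| Family, three contrasts each | Tests | At 0.05/3 | At 0.01 |
|---|---|---|---|
| HbA1c, one visit | 3 | 4.4% | 2.7% |
| HbA1c, both phase ends | 6 | 6.9-8.6% | 4.4-5.4% |
| Three outcomes, one visit | 9 | 9.0-12.7% | 5.7-7.9% |
| HbA1c and activity, both phase ends | 12 | 10.4-16.4% | 6.7-10.4% |
| Three outcomes, both phase ends | 18 | 13.0-23.6% | 8.5-15.2% |

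HbA1c and activity at a single visit also make 6 tests and have the same rates as the second row.

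**4. Can all three outcomes be tested?** Section 4.1.b lists VO2 max among the measurements. Its schedule, however, marks the exercise stress test at baseline only and has no VO2 max row at a follow-up visit. A change in VO2 max may therefore not be testable, and the rows without it may be the relevant ones.

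**The case against.** Much can be said for the protocol.

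- It does address multiplicity. A reader might infer that 0.05/3 is the only adjustment, limited to one outcome. The documents do not support that: section 6.2.a sets P<0.01 because of the number of models, and section 6.2.b reuses 0.05/3 for two Aim 2 outcomes.
- Both phase ends come from section 2.3.b, which is headed as secondary. Two of its hypotheses are also restricted by adherence, for example "By the end of Phase 1, experimental study participants (Arm 1 & Arm 2) who adhered to their group exercise schedule". Counting all of them as routes to primary success ignores the heading.
- Section 2.3.b states two comparisons per phase end (exercise arms against usual care, thrice-weekly against weekly), not three. If the exercise arms are pooled, three outcomes at one visit give 8.7-9.6% at 0.05/3 and 5.4-5.9% at 0.01 (correlation 0.5 to 0).
- The first research question, "Does a thrice-weekly, structured exercise regimen have greater reduction in HbA1c than a weekly contact exercise regimen", is followed at once by a question about usual care. Its position does not contradict the primary hypothesis.
- Testing order is commonly left to the SAP, which is not shown.

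These points limit the error rates and remove any claim that multiplicity was ignored. They do not remove the conflict over what is primary. An SAP could only choose between statements that the protocol itself makes, and section 2.3.b uses the primary label for outcomes that sections 2.1.d and 6.2.a call process measures. The mismatch between 0.01 and 0.05/3 also stands.

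**Conclusion.** The point holds as an internal contradiction: three accounts of what is primary, no primary visit, and two unreconciled significance levels. It should be fixed.

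The error rates are conditional. If any one success on the three outcomes counted, over three pairwise contrasts, the family-wise error would be about 9-13% at 0.05/3 or 6-8% at 0.01 at one visit. Over both phase ends it would be about 13-24% or 8-15%. HbA1c alone at one visit is controlled at either level, and HbA1c at both phase ends is about 5% at 0.01. A reader might infer that the trial's false-positive rate is 13-20%. The documents do not support that as a property of the plan: no section says any one success counts, the phase-end hypotheses are headed secondary, and such a range mixes the two thresholds for an 18-test family.

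The power shortfall does not depend on those assumptions. If the trial has 80% power at 0.05/3, it has about 75% at P<0.01.

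**What to change.** In sections 2.3.a, 2.3.b, 6.2.a and 6.2.b:

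- Name change in HbA1c as the single primary outcome at one stated visit. The 6-month visit, at the end of the intervention, is the natural choice, but the sample size is tied to no visit, so the sponsor must confirm it.
- Name the three pairwise arm contrasts as the primary family.
- Call VO2 max and self-reported activity process measures throughout, and state whether VO2 max is measured after baseline.
- Label other visits and Aims 2 and 3 secondary or exploratory, and reword the opening of section 6.2.b to match.
- Use one significance level for the primary family. Either apply 0.05/3 (or Holm) to it and limit P<0.01 to the other models, or keep 0.01 and restate the power as about 75%.

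The cost is wording only, with no extra patients or data. The downside is that success on activity, fitness or 30-month results alone could no longer be reported as a primary finding. The change should be made before outcome data are seen.
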